## 2.1 Sub-study Summary:

| Title:                         | Qualitative Interview Study                                                                                                                                                                                                                                                                                 |                                                                             |
|---------------------------------------|-------------------------------------------------------------------------------------------------------------------------------------------------------------------------------------------------------------------------------------------------------------------------------------------------------------|-----------------------------------------------------------------------------|
| Sample size:                   | Trial participants:
50 parent-child dyads or until saturation, whichever comes first
Trial decliners:
10 parent-child dyads                                                                                                                                                                        |                                                                             |
| Sub-study Inclusion Criteria : | Parent-child dyads eligible to take part in the main trial will also require: 
 
Ability of parent and child to speak conversational English.
 
Additional consent to main trial: Consent of parent to participate and for their child to participate
 
 |                                                                             |
| Patient Sub-study Duration:    | 12 months                                                                                                                                                                                                                                                                                                   |                                                                             |
| Overall Sub-study Duration:    | 60 months                                                                                                                                                                                                                                                                                                   |                                                                             |
|                                       | Objective                                                                                                                                                                                                                                                                                                   | Outcome Measures                                                            |
| Primary:                       | To explore and capture qualitative information relating to children's and their parents' experiences of the decisions and choices they make regarding the treatment and management of RE                                                                                                                    | Face-to-face/telephone or skype interviews (audio recorded and transcribed) |

Figure 1: Schematic of Trial Design

[figure not shown]

\* The trial will be open to recruitment for 36 months. Follow up will be carried out on those recruited during the recruitment period and for 12 months after recruitment is closed. Therefore, if a patient joins the trial in the first month of opening to recruitment, the follow-up will be up to 48 months. In contrast, if the patient joins the trial just before closing recruitment, the follow-up will only last a maximum of 12 months.

## 3 INTRODUCTION

### 3.1 Background

#### 3.1.1 Rolandic Epilepsy

RE, also known as benign epilepsy of childhood with centro-temporal spikes (BECTS), is the most common epilepsy in childhood, with an incidence of up to 21 per 100.000 children aged 15 years and under. The onset of seizures is between 3 and 12 years, and remission almost always occurs by adolescence. Seizures typically occur during sleep or drowsiness, are brief and involve unilateral sensorimotor symptoms (e.g. numbness, tingling, drooling) of the pharynx, tongue, face, lips and sometimes hand. The affected side may alternate and seizures may infrequently become secondarily generalised. Neurodevelopmental disorders are very common (40%) and include speech sound disorder, language impairment and reading disability, all of which usually precede seizures and aggregate among relatives. Attention deficit hyperactivity disorder (ADHD) and migraine without aura are also strong but less frequent (10%) associations.

#### 3.1.2 The Clinical Trial

This clinical trial is the major component of a programme of work on childhood epilepsy interventions and outcomes. Complementary work packages include the development of a core outcome measure set (Work Package 1); qualitative methods (Work Package 2); and the generation of an online parent-based sleep (PBS) intervention (also referred to as sleep behaviour intervention) for use in the trial (Work Package 3). We will conduct a pragmatic, unblinded, randomised 3x2 factorial trial of anti-epileptic drug (AED) (carbamazepine or levetiracetam or no AED) and sleep behaviour intervention or standard care, to evaluate their comparative effect on seizures, sleep problems, learning and patient-centred outcomes. In addition, engagement via patient and public involvement (PPI) advisory panel(s) will ensure that each stage of the programme is informed by the perspectives of children with rolandic epilepsy (RE) and their parents. An embedded economic evaluation will assess the cost-effectiveness of each intervention, from the perspective of the NHS and PSS.

### 3.2 Rationale

#### *Choice of Anti-Epileptic Drug (AED)*

The evidence base for treatment in childhood epilepsies in general, and for RE in particular, is scant (4, 5) and the quality of available evidence is judged in an Health Technology Assessment (HTA) monograph by the International League Against Epilepsy, and by National Institute for Health and Care Excellence (NICE) as “poor” (4, 6, 7). A Cochrane review in RE identified four randomised controlled trials (RCTs) of AED treatment in 262 children with RE. One good quality placebo-controlled RCT showed that sulthiame (not widely available in UK) is effective for seizure remission in the short-term (3-6 months), although the precision of the effect estimate was uncertain due to small sample size (5). Three low quality open-label AED comparative studies did not show differences in effectiveness or side-effects (5) amongst different AEDs (levetiracetam vs oxcarbazepine; clobazam vs carbamazepine; topiramate vs carbamazepine). The review concludes “there is insufficient evidence about the medium to longer effects on seizure control, the optimum AED and the effects of AED on cognition [...] there is a need for good quality RCTs to address these questions [...]”.

#### *Practice*

Carbamazepine, a first-generation AED, is the current NICE standard treatment for RE (7). Our national survey confirmed that UK paediatricians prescribed carbamazepine as first-line choice (80%),

although there was great variability of choice amongst the remainder (8). Importantly, the survey revealed that in 40% of cases paediatricians treat RE patients conservatively, i.e. without drugs, as advocated in older textbooks (8). Carbamazepine has never been compared against no-treatment in RE, and in view of the AED's known cognitive adverse effects, it is important to know whether any benefit in terms of seizure control offsets its impact on children's learning. Second-generation AEDs (levetiracetam, lamotrigine, gabapentin, but not topiramate) have fewer cognitive side-effects in healthy adult volunteers than first-generation (carbamazepine, oxcarbazepine, valproate, phenobarbital, phenytoin) (9-15); and the International League Against Epilepsy judges only levetiracetam, of these second-generation AEDs, to have potential efficacy in RE (4). A generic version of levetiracetam was released in 2014 with comparable treatment cost to carbamazepine. Although not licensed for monotherapy in children, it is in widespread off-label use and is judged to be efficacious and well-tolerated (16). Thus levetiracetam would make an ideal and potentially superior comparator and has not been assessed head-to-head with carbamazepine in childhood epilepsy. NICE also made a specific research recommendation ([CG137:4.1]) for "levetiracetam to be evaluated as a first-line monotherapy in a prospective RCT [...] including *quality-of-life and cognitive outcomes*". The trial would complement the ongoing HTA-funded Standard and New Antiepileptic Drugs (SANAD-II) trial of levetiracetam, zonisamide and lamotrigine (Arm A: focal seizures), which has principally recruited adults (<http://www.nets.nihr.ac.uk/projects/hta/0914409>). The economic evaluation will address uncertainties and gaps in the evidence with respect to determining which interventions are cost-effective for use in practice and for broader adoption by the NHS.

### *Design considerations*

We have assessed the feasibility of the proposed RCT among 132 UK paediatricians who are local leads for epilepsy management, and they expressed both equipoise over the benefits of treatment vs no-treatment in RE and acceptance to randomise to a no-treatment arm; they also indicated carbamazepine and levetiracetam as their preferred active comparators. A pragmatic design is chosen to provide guidance on decisions for clinical care contexts. Although we will capture seizure data, we will also give prominence to patient-relevant and learning outcomes as these are likely to relate to quality-of-life. In-depth interviews from the embedded qualitative study will explore and capture experiential data.

### *Sleep Intervention*

Despite the frequency of sleep problems in children with epilepsy (and other neurodevelopmental disorders), clinicians in the UK receive little training on the subject (17, 18). This lack of training, and lack of epilepsy-specific evidence-based interventions, combined with a focus on seizure control means that sleep problems are rarely addressed in routine clinical practice. Even if sleep problems were a management target, the lack of any evidence-based resources for intervention is a barrier to such implementation. The PBS intervention offers parents education about normal sleep, advice about sleep-promoting practices and targeted strategies parents can employ to help their children to "learn" an appropriate set of sleep behaviours/habits and/or to unlearn inappropriate sleep behaviours.

The PBS intervention will include several evidence-based behaviour-change techniques including: extinction (unmodified or graduated with parental presence); scheduled wakings; positive routines with or without response cost; bedtime fading and positive reinforcement.

### 3.2.1 Risk and Benefits

The recruiting clinician will discuss the potential risks and benefits with patients and their parents/primary carers prior to trial entry and they will be outlined in the patient and parent/guardian information leaflets. Young women of child-bearing age will not be excluded from the trial because equipoise similarly exists about the merits of treatment and non-treatment of seizures in RE in this group. Monitoring of this group will be as in standard clinical practice with no mandatory pregnancy testing. Participants should receive individual counselling, guidance on contraception, interactions with contraceptive medications and the risks of teratogenicity as in routine medical practice.

The trial randomisation arms represent clinical pathways in current practice and as such the risks of participating in the trial are no greater than those encountered in standard care. The main risk of the CASTLE trial is that patients may be allocated to a treatment that on final analysis is found to be less effective than or have a higher adverse reaction (AR) rate than another. However, participants will be switched from their allocated treatment if a decision is made with the treating physician that seizure control is inadequate or adverse reactions (ARs) are unacceptable. For participants involved in the qualitative component, any concerns raised within the interviews will be reported as appropriate.

### 3.2.2 Known Potential Benefits

Patients recruited into the trial will receive standard NHS care during the conduct of the trial. The main potential benefit is that patients might receive treatment with a drug which is more effective than no AED. Patients might also receive benefit from the PBS intervention in terms of improved sleep compared to standard treatment. Patients may also feel benefit from a regular and rigorous follow-up schedule.

## 3.3 Objectives and Outcome Measures/Endpoints

Table 1: Summary of Objectives, Outcome Measures and Timepoints

| Primary Objectives                                                                                                               | Outcome Measures                                          | Timepoint(s) of evaluation of this outcome measure                                   |
|----------------------------------------------------------------------------------------------------------------------------------|-----------------------------------------------------------|--------------------------------------------------------------------------------------|
| To determine if carbamazepine or levetiracetam are superior to no AED with respect to time to 6-month seizure remission.         | Time to 6-month seizure remission based on seizure report | 3, 6, 12 months and annually thereafter - 'when was last seizure' question in clinic |
| To determine if a PBS intervention is superior to standard care with respect to 3-month sleep problem frequency measured by CSHQ | Total sleep problem score as measured by the CSHQ         | At baseline and 3 months                                                             |
| Primary Economic Objective †                                                                                          | Outcome Measures                                          | Timepoint(s) of evaluation of this outcome measure                                   |
| To estimate the cost-utility of carbamazepine, levetiracetam and PBS                                                             | Total costs; and quality-adjusted life years (QALYs)      | Resource use and utility questionnaires at baseline, 3, 12 months and annually       |

† This has no implications for sample size calculation

|                                                                                                          |                                                                                                                                                                                     | thereafter; routine hospital data at the end of the trial                        |
|----------------------------------------------------------------------------------------------------------|-------------------------------------------------------------------------------------------------------------------------------------------------------------------------------------|----------------------------------------------------------------------------------|
| Secondary Objectives                                                                              | Outcome Measures                                                                                                                                                             | Timepoint(s) of evaluation of this outcome measure                        |
| To compare time to treatment failure due to inadequate seizure control or unacceptable adverse reactions | Time taken from randomisation to decision by child, parent or treating physician to be withdrawn from treatment due to inadequate seizure control or unacceptable adverse reactions | 3, 6,12 months and annually thereafter                                           |
| To compare time to treatment failure due to inadequate seizure control                                   | Time taken from randomisation to decision by child, parent or treating physician to be withdrawn from treatment due to inadequate seizure control                                   | 3,6,12 months and annually thereafter                                            |
| To compare time to treatment failure due to unacceptable adverse reactions                               | Time taken from recruitment to decision by child, parent or treating physician to be withdrawn from trial due to unacceptable adverse reactions                                     | 3,6,12 months and annually thereafter                                            |
| To compare time to first seizure                                                                         | Time to first seizure based on seizure report                                                                                                                                       | 3,6,12 months and annually thereafter 'when was last seizure' question in clinic |
| To compare time to 12-month remission from seizures                                                      | Time to 12-month seizure remission based on seizure report                                                                                                                          | 3,6,12 months and annually thereafter 'when was last seizure' question in clinic |
| To determine if a PBS intervention is superior to standard care                                          | Total sleep problem score as measured by the CSHQ                                                                                                                                   | At 12 months and annually thereafter                                             |
| To compare measures of cognition across the different treatment groups                                   | Total score in three chosen assessments delivered by CANTAB iPad Neuropsychological battery                                                                                         | At baseline, 3 and 12 months and annually thereafter                             |
| To compare Health Related Quality of Life across the different treatment groups                          | CHEQOL score change (1)                                                                                                                                                             | At baseline and 12 months and annually thereafter                                |
| To compare measures of children's behaviour across the different treatment groups                        | Total score on strengths and difficulties questionnaire (SDQ)                                                                                                                       | At baseline and 12 months and annually thereafter                                |
| To identify any adverse reactions and their rate                                                         | Records of adverse reactions                                                                                                                                                        | Adverse reactions at 3,6,12,24 months and annually thereafter in clinic          |

|                                                                                                           |                                                                                                                                       |                                                                                                         |
|-----------------------------------------------------------------------------------------------------------|---------------------------------------------------------------------------------------------------------------------------------------|---------------------------------------------------------------------------------------------------------|
| To estimate child health utilities and QALYs across the different treatment groups                        | Score changes in:
1. CHU9D (2)
2. EQ-5D-Y                                                                                       | Questionnaire at baseline, 3, 12 months and annually thereafter                                         |
| To estimate health utilities and QALYs across parents in the different treatment groups                   | EQ-5D-5L score change                                                                                                                 | Questionnaire at baseline, 3, 12 months and annually thereafter                                         |
| To compare parenting self-efficacy across the different treatment groups                                  | Score changes in:
1. PSAM (3)                                                                                                      | Questionnaire at baseline, 3, 12 months and annually thereafter                                         |
| To compare sickness related school absences across the different treatment groups                         | Total sickness related school absences (days)                                                                                         | 3,6,12 months and annually thereafter 'sickness related school absences' question in clinic             |
| To determine the costs to the NHS                                                                         | 1. Resource use questionnaire
2. Patient Level Information and Costing System (PLICS) data
3. Hospital Episode Statistics (HES) | Resource use questionnaire at 3, 12 months and annually thereafter

PLICS and HES at end of trial |
| Other Objectives                                                                                   | Outcome Measures                                                                                                               | Timepoint(s) of evaluation of this outcome measure                                               |
| To determine which sleep parameters change in primary carer and child dyads in different treatment groups | Summary of actigraphy variables (total sleep time/sleep latency/sleep efficiency) averaged over a 1-week period                       | 1 week actigraphy (arranged centrally via Oxford unit) at baseline, 3 and 12 months                     |

|                                                                                                                                                                                          |                                                                             |                                                           |
|------------------------------------------------------------------------------------------------------------------------------------------------------------------------------------------|-----------------------------------------------------------------------------|-----------------------------------------------------------|
| Sub-study Objective                                                                                                                                                               | Outcome Measures                                                     | Timepoint(s) of evaluation of this outcome measure |
| To explore and capture qualitative information relating to children's and their parents' experiences of the decisions and choices they make regarding the treatment and management of RE | Face-to-face/telephone or skype interviews (audio recorded and transcribed) | 2-4 weeks, 6 months and 12 months after randomisation     |

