**8.1.2 Schedule for Follow-up**

The expected duration of follow-up for each participant is between a minimum of 12 months and a maximum of 48 months, depending on the time of recruitment. All participants will be followed up whether they are still taking their allocated treatment or not. Where participants default from hospital follow-up, additional information will be sought at the end of the trial from GPs who will be the main prescribers of AEDs in this trial, and where necessary participants will be contacted directly for follow up information.

Participants will be followed up as per routine clinical practice and typically at 3, 6, and 12 months and annually thereafter, where applicable. Participants will be seen at other times as clinically indicated.

A visit window for the 3 month visit of +/- 2 weeks is allowed. Visit windows are not prescribed for the 6, 12 months or annual visits after that. A delegated member of the research team should complete the 'follow-up CRF' for the 3, 6, 12 month and annual visits. The visit which occurs at the nearest timepoint will be taken to be the record of the 3, 6, 12 months or other annual visits from randomisation.

In the event of an early trial termination, the schedule for follow up activities (including actigraphy and qualitative interviews) will be shortened accordingly to 6 months post-randomisation. This will occur following agreement by the TMG, IDSMC and Sponsor.

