### **8.5.2 Stopping the Allocated Trial Intervention**

Participants may be withdrawn from treatment for any of the following reasons:

- a. Appropriate adult who provided consent withdraws consent (or, where applicable, the minor participant withdraws assent).
- b. Unacceptable toxicity.
- c. Intercurrent illness preventing further treatment.
- d. Any change in the participant's condition that justifies the discontinuation of treatment in the clinician's opinion.

If a participant or the adult who provided consent on their behalf wishes to stop trial treatment, follow-up will continue unless the participant or appropriate adult explicitly also wishes to stop this. Centres should explain the importance of remaining on trial follow-up, or failing this, of allowing routine follow-up data to be used for trial purposes.

Note that if the allocated treatment is stopped due to a safety event, the participant will be given appropriate care under medical supervision until the symptoms of any safety event resolves or the participant's condition becomes stable.

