## **9.2.3 Dose Modifications and Management of Toxicity**

Dose modifications and management of toxicity will be undertaken by the PI or delegated medically qualified physician according to usual practice. The aim of treatment will be to control seizures with a minimum effective dose of drug. This will necessitate dosage modification if further seizures or ARs occur as is usual clinical practice. The decision to discontinue allocated trial treatment is at the discretion of the PI or delegated medically qualified physician and participant/their parent/primary carer. Treatment may be discontinued at any point during the trial period for reasons such as

inadequate seizure control, unacceptable ARs, or any change in the participant's condition that the physician believes warrants a change in medication. Any changes in medication must be documented on the appropriate follow up CRF along with the justification for those changes. If a participant's treatment stops prematurely, the reason for discontinuation should be recorded on the premature discontinuation on the trial treatment CRF and the participant should still be encouraged to attend follow up visits for the remainder of the trial. Any changes in trial treatment dosage must be documented on the trial treatment CRF along with the justification for those changes.

At the end of trial participation the participants may continue their treatment as per local policy.

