A similar strategy will be used for the analysis of secondary time to event outcomes. For time to treatment failure, further analysis will be undertaken to assess the two main reasons for treatment failure - inadequate seizure control and unacceptable adverse effects. To allow for possible dependence between the different withdrawal risks, cumulative incidence analyses will be presented (34).

The Haybittle-Peto approach will be employed for each interim analysis, with 99.9% confidence intervals calculated for interim analysis effect estimates. The final analysis will be undertaken at the end of the trial when all participants have a minimum 12 months follow-up data and 95% confidence intervals will be calculated.

QOL data will be analysed longitudinally to explore between treatments changes in scale scores over time, taking account of baseline QOL.

Qualitative interview data will be analysed using an interpretive, reflexive and conceptual analytical approach. Data will be thematically analysed in discrete sets (e.g., the trial group and the non-trial groups, different treatments/management, different responses/experiences), and parents/primary carers' and children's transcripts will be analysed separately before considering each dyad and prior to synthesis of all the data.

For the analysis of safety events, all participants who received any amount of each trial drug will be included in the safety analysis dataset in the treatment group they actually received. All safety events reported by the clinical investigators will be presented, identified by treatment group. Safety events will be grouped according to a pre-specified coding system and tabulated. The number (and percentage) of participants experiencing each safety event, and the number (and percentage) of occurrences of each safety event will be presented. No formal statistical testing will be undertaken.

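### Time to treatment failure due to unacceptable adverse reactions is defined as leaving the trial, not stopping treatment, which conflicts with its own objective, the other two failure outcomes and sections 8.2.1 and 11.5.1

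*Protocol*

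**What the plan says.** Section 2 (Protocol Summary) and section 3.3 (Table 1) each list three treatment-failure outcomes.

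- **Composite.** It is timed from randomisation, and the event is a decision for the child to be "withdrawn from treatment due to inadequate seizure control or unacceptable adverse reactions".
- **Seizure control.** "Time taken from randomisation to decision by child, parent or treating physician to be withdrawn from treatment due to inadequate seizure control".
- **Adverse reactions.** The objective column names this as time to treatment failure, but the outcome column reads "Time taken from recruitment to decision by child, parent or treating physician to be withdrawn from trial due to unacceptable adverse reactions".

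Elsewhere the protocol separates stopping treatment from leaving the trial. Section 8.5.2 deals with stopping the allocated intervention and says that "follow-up will continue unless the participant or appropriate adult explicitly also wishes to stop this". Section 8.5.3 deals with complete withdrawal, which has its own Withdrawal CRF. Section 8.1.2 states that "All participants will be followed up whether they are still taking their allocated treatment or not". Section 9.2.3 adds that, after premature discontinuation, "the participant should still be encouraged to attend follow up visits for the remainder of the trial".

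Section 8.2.1 says how time to treatment failure is to be calculated: from the date on which the randomised AED failed and the reason for failure, recorded at clinic visits. Section 11.5.1 then divides treatment failure by its two main reasons and states: "To allow for possible dependence between the different withdrawal risks, cumulative incidence analyses will be presented".

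**The concern.** A composite and its cause-specific components should share one time origin and one kind of event, so that each composite event is assigned to one cause. Here one of the two components has a different origin and, more importantly, a different event. The protocol tries to keep children in follow-up after they stop a drug, so the event named in the definition is not the usual result of an unacceptable reaction.

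What is at stake is the trial's time-to-event measure of tolerability. An analyst or reader who works from Table 1 would build an endpoint that misses children who stop a drug because of a reaction and stay in the trial. The error has a direction: the better the retention after stopping, the fewer tolerability failures the component records.

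**Working it through.** The protocol gives no figure to reproduce for this outcome. The check is a comparison of definitions, followed by what the literal wording implies.

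**1. Definitions side by side (section 2 and section 3.3, Table 1)**

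| Outcome | Clock starts | Event |
|---|---|---|
| Composite | Randomisation | Withdrawal from treatment, either reason |
| Inadequate seizure control | Randomisation | Withdrawal from treatment |
| Unacceptable adverse reactions | Recruitment | Withdrawal from trial |

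The third row differs in both columns. The wording is the same in both places and is current text, not part of the amendment chronology.

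**2. Are the two events interchangeable?** No. Sections 8.5.2 and 8.5.3 treat them separately, and sections 8.1.2, 8.5.2 and 9.2.3 all make continued follow-up the default once treatment stops.

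**3. A child stops the allocated drug for a reaction and keeps attending.**

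- Composite: an event, at the date of the decision to stop.
- Seizure-control component: not an event.
- Adverse-reaction component, read literally: not an event, because the child has not left the trial.

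This child is a composite failure with no cause assigned. A child who stops the drug and later leaves the trial for the same reaction would be counted, but at the later date.

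**4. Size of the under-count.** Let *a* be the number in an arm who stop treatment for a reaction, and *b* the number of those who also leave the trial for it. The literal component counts *b* and misses *a* − *b*, a fraction 1 − *b*/*a*. This fraction is 0 if every such child leaves the trial and 1 if none does. The protocol gives neither *a* nor *b*, so the range cannot be narrowed. The retention provisions push *b* down and the fraction up.

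**5. Time origin.** Section 8.1.1 lists consent, baseline assessments and randomisation all under visit 1. Whatever moment recruitment is taken to mean, it should normally lie close to randomisation. This difference is untidy but has little numerical effect.

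**6. Consistency with data collection and analysis.** Section 8.2.1 collects the date and reason of AED failure and says that these give time to treatment failure. Section 11.5.1 splits that outcome by reason. Both rest on treatment. Neither uses the Withdrawal CRF of section 8.5.3, which is what the literal definition would need. The outcome entry is therefore at odds with the sections that put it into operation.

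**The case against.** The strongest reply is that this is a drafting slip and the rest of the protocol shows the intention. The objective in the same table row says treatment failure, section 8.2.1 bases the calculation on failure of the randomised AED, and section 11.5.1 analyses reasons for treatment failure. An analyst who follows those sections gets the right endpoint, and no data are lost. All of that stands, and it limits the seriousness of the point. It does not remove the point. Table 1 is where the outcome is formally defined, and the entry there and in the summary is wrong rather than left open. A statistical analysis plan (not available here) could repair it only by departing from the stated definition.

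Three stronger readings are tempting, and the protocol does not support them.

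- A reader might infer that children who stop a drug and stay in follow-up are never counted as failures. They are counted in the composite, and their date and reason for failure are recorded. Only the adverse-reaction component misses them, and only on its literal wording.
- A reader might infer that the planned cumulative incidence analysis is invalid. As section 11.5.1 describes it, the analysis starts from treatment failure and splits it by reason, which gives components consistent with the composite. The Table 1 definition contradicts that analysis but does not show it to be unsound.
- A reader might want a percentage for the failures missed. Any such figure would need assumed counts for both *a* and *b*, and the protocol supplies neither.

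**Conclusion.** The definition of the adverse-reaction failure outcome is wrong as written, in two places. It names the wrong event for its stated objective and conflicts with the two companion outcomes and with sections 8.2.1 and 11.5.1. Taken literally, it under-counts tolerability failures and breaks consistency with the composite. The direction of the error follows from the text, given that some children who stop for a reaction stay in the trial, which the protocol makes the default. Its size cannot be derived. The substantive fault is trial versus treatment; recruitment versus randomisation is minor.

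Severity is moderate. One component of a secondary outcome family is affected. The composite, the seizure-control component, both primary outcomes and the sample size are untouched.

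**What to change.** In section 2 and in section 3.3, Table 1, change the adverse-reaction entry in two respects: start the clock at randomisation instead of recruitment, and make the event withdrawal from treatment instead of withdrawal from trial. The entry then has the same form as the other two failure outcomes and agrees with section 8.2.1.

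The cost is one line of wording in each of two places. No change to the CRF, visit schedule, sample size or primary analyses is needed, because date and reason of AED failure are already collected. The change should be made before any analysis by reason for failure is run, and the statistical analysis plan should be checked to see that it carries the corrected definition.
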